**Figure 2 F2:**

The sample size calculation formula.

### Therapeutic drug

2.4

#### Oral Chinese patent medicine commonly used in CHD angina pectoris

2.4.1

Shexiang Baoxin Pill, Tongxinluo Capsule, Tongmai Yangxin Pill, Xuefu Zhuyu Capsule, and Qishen Yiqi Dropping Pill.

#### Conventional western medicine for CHD angina pectoris

2.4.2

Antiplatelet drugs, statins, beta blockers, calcium channel blockers, angiotensin converting enzyme inhibitor, angiotensin II receptor antagonists, and so on.

### Adverse reactions

2.5

In this study, the adverse reactions of drugs (Chinese patent medicine and conventional western medicine) studied are detailed in the drug instructions.

### Regulations on combined use of drugs

2.6

Patients with CHD angina pectoris can be treated with the original scheme before admission during the study period, and the admission period is 2 weeks, so that the patient's condition is stable and meets the admission criteria.

During the study period, for patients with hypertension, diabetes, hyperlipidemia, and other diseases, the antihypertensive, hypoglycemic, and lipid-lowering treatment schemes before admission can be maintained. The name, dosage, and usage of the drugs are recorded in detail in the study medical records. It is forbidden to adjust the dosage and usage of β-receptor blockers, calcium ion antagonists, and other drugs that affect the curative effect of CHD angina pectoris.

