1.Resting angina pectoris: Angina pectoris attack at rest, and the duration is usually more than 20 minutes.2.Initial angina pectoris: New angina pectoris occurred within 1 month, which may be characterized by spontaneous and exertional episodes, with pain ranking above grade III.3.Aggravated exertional angina pectoris: Previous history of angina pectoris, aggravation of angina pectoris in the past month, frequent attacks, prolonged time or reduced pain closure (angina pectoris grade at least increased by grade I, or at least reached grade III).4.Variant angina pectoris: Usually spontaneous. It is characterized by transient ST segment elevation, most of which spontaneously relieves and does not develop into myocardial infarction, but a few of which can develop into myocardial infarction. Atherosclerotic plaque leads to local endothelial dysfunction and coronary artery spasm, which are the causes of the disease. Nitroglycerin and calcium antagonist can relieve it.

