#### Inclusion criteria

2.2.3

The inclusion criteria were as follows:

1.Voluntary participation, understanding, and signing of informed consent form.2.The age ranged from 35 to 75 years old and gender is not limited.3.For patients with angina pectoris of CHD in the inpatient department or outpatient department of cardiology, the diagnosis of angina pectoris conforms to the relevant guidelines issued by ACC/AHA, Chinese Society of Cardiology and Chinese Journal of Cardiology.4.For patients who meet the standard of drug therapy, the exposed group is treated with Chinese patent medicine combined with conventional western medicine, while the nonexposed group is treated with conventional western medicine alone.

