#### Exclusion criteria

2.2.4

The exclusion criteria were as follows:

1.Patients who are combined with other cardiac diseases, neurosis, climacteric syndrome, hyperthyroidism, cervical spondylosis of spinal cord or vertebral artery type, gastroesophageal reflux disease or hiatal hernia, and other diseases that may cause chest pain.2.Angina pectoris patients with serious and uncontrollable symptoms, suffering from acute myocardial infarction, heart failure, myocarditis, cardiomyopathy, severe heart valve diseases, liver failure or renal failure, malignant tumor, severe metabolic diseases, and other major diseases.3.Women who are pregnant or lactating or women are in childbearing age with fertility requirements.4.Patients with a mental disorder or cognitive dysfunction.5.Patients who have participated in other trials within the past 3 months.6.Patients with a history of allergy or with a known allergy to the study drug.7.Patients who are expected to poor compliance and unpossible regular visits.8.Patients with no current address or incomplete current address without contact telephone number.9.Patients who are unable to participate in the study, as judged by the investigator.

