### Follow-up time point

2.7

Patients need to be hospitalized for 2 weeks as the introduction period and whether to enter the group is determined according to the treatment and medication conditions of the patients. The follow-up time points were 0th, 4th, 12th, 24th, and 48th weeks. The main curative effect, secondary curative effect, and concomitant medication changes of patients were observed.

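### Section 2.6 forbids adjusting background angina drugs and gives no exception for worsening angina, intolerance or a cardiovascular event

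*Protocol article*

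**What the plan says.** Section 2.6 has two paragraphs. The first lets patients continue their pre-admission regimen and describes a 2-week admission period meant to stabilise them. The second opens "During the study period, for patients with hypertension, diabetes, hyperlipidemia, and other diseases" and allows existing treatment for those conditions to be maintained, with drug details recorded. It ends with the rule at issue: "It is forbidden to adjust the dosage and usage of β-receptor blockers, calcium ion antagonists, and other drugs that affect the curative effect" (the effect on angina is meant).

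The restricted drugs belong to the study's background care. Section 2.4.2 lists conventional western medicine as "Antiplatelet drugs, statins, beta blockers, calcium channel blockers, angiotensin converting enzyme inhibitor, angiotensin II receptor antagonists, and so on". Under section 2.2.3, "the nonexposed group is treated with conventional western medicine alone", and the exposed group receives the same kind of care plus a Chinese patent medicine.

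On timing, section 2.7 states "The follow-up time points were 0th, 4th, 12th, 24th, and 48th weeks" and adds "The main curative effect, secondary curative effect, and concomitant medication changes of patients were observed". The Discussion (item 2) presents the strictness of the drug rules as a strength of the design.

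**The concern.** The rule is an outright prohibition on adjusting drugs that angina patients commonly need adjusted. A physician who follows it could not raise a beta blocker dose for worsening angina, lower it for intolerance, or revise the regimen after an infarction or revascularisation.

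Two things are at stake. The first is patient care: followed literally, the rule withholds needed treatment changes in both groups. The second is what the study estimates. The stated comparison is with conventional western medicine, and in practice that is adjusted to the patient's course. If doses are frozen, the result applies to a Chinese patent medicine added to a fixed background regimen, which is a narrower question.

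**Working it through.** The plan gives no figure on this point to reproduce. The check sets the relevant sections side by side.

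**1. Is there an exception?** Section 2.6 has none. Section 2.5 acknowledges adverse reactions to both kinds of drug but only points to the drug instructions. No other section of the article gives a rescue, dose-modification or discontinuation rule.

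**2. Which patients and drugs?** The ban sentence names no patient group. It covers two drug classes by name and then any other drug that affects angina. Its paragraph opens with comorbid patients, so it could be read as limited to them. On that reading the exception is still missing for those patients, and the Discussion says CHD is often accompanied by such conditions.

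**3. For how long?** The ban sentence names no period. Its paragraph opens with a reference to the study period, and the 2-week admission period is named separately in the same section. The natural reading is therefore that the ban lasts through follow-up. On that reading only:

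- duration after entry = week 48 − week 0 = 48 weeks;
- time remaining after an event at week 4 (an illustrative date) = 48 − 4 = 44 weeks.

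**4. Are needed changes foreseeable?** Yes, for three reasons.

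- The diagnostic criteria in section 2.2.1 include unstable types, such as aggravated exertional angina, described by "aggravation of angina pectoris in the past month, frequent attacks, prolonged time". Section 2.2.4 excludes "Angina pectoris patients with serious and uncontrollable symptoms", and the 2-week period stabilises the others. Both act at entry and do not cover worsening later.
- The main events in section 2.8.4 are infarction and revascularisation, after which drug regimens normally need review.
- Section 2.8.6 still collects death and cardiovascular readmission at weeks 24 and 48. Follow-up therefore continues after a nonfatal event and, on the natural reading, so does the ban.

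**5. Does the rule fit the rest of the article?** Section 2.7 observes medication changes, section 2.11.1 plans an analysis of concomitant medication, and the Introduction justifies a cohort partly because it can follow treatment that shifts over time. All three expect change, while section 2.6 forbids it for the drugs most relevant to angina.

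**The case against.** The strongest reply is that this is a condensed article. Rescue and dose-modification rules often sit in the full protocol, so their absence here proves nothing about the study. That would settle the matter if section 2.6 were silent, but it prints a prohibition. If the full protocol contains an exception, the article's sentence misstates the rule and should carry the exception. It would be too strong to conclude that no exception exists anywhere; the article alone cannot show that.

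A second reply concerns scope. The reference to the study period belongs to a different sentence, and the ban may only qualify the permission given for comorbidity treatment, since beta blockers and calcium antagonists also lower blood pressure. This stands as a real ambiguity. A reader might infer that every patient is certainly bound for all 48 weeks, but the text does not establish that.

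A third reply is that the article plainly expects drug changes: it observes them, plans to analyse concomitant medication, and stratifies by drug usage and treatment duration (section 2.11.2, item 6). But recording or analysing a change does not permit it. These provisions show that the article pulls in two directions, which is a reason to clarify section 2.6.

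Finally, holding background therapy stable is a recognised design choice and is deliberate here. That stands, and the aim can be kept. What does not follow from it is a ban without allowance for clinical need.

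**Conclusion.** The point holds as a fault in a stated rule. Section 2.6 forbids adjusting angina drugs without exception. Followed as written, it would bar clinically needed changes, make the comparator a fixed regimen, and conflict with section 2.7 and the Introduction. The 48-week duration is the natural reading but not the only one.

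No size or direction of bias is claimed. The article does not say how many patients would need a change, and the rule is not limited to one group. A reader might infer that the ban pushes patients with worsening angina towards revascularisation or readmission and so inflates the counted outcomes. That is plausible, but nothing in the article shows it. A reader might also infer that patients whose drugs are changed are withdrawn or dropped from the analysis. The article does not say so; it leaves their handling unstated.

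The conclusion assumes that sites would apply section 2.6 literally. If they would not, the rule would be broken mainly for patients with a clinical need, which is another reason to write the exception down.

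**What to change.** In section 2.6, keep background antianginal therapy stable where possible and add wording such as: *Changes needed for worsening angina, intolerance or a cardiovascular event are allowed in both groups. Drug, dose and date are recorded. The patient stays in follow-up and in the main analysis.* State the period and the patients to which the stability rule applies, so that the ambiguity of scope goes too. Describe the changes by group in the concomitant-medication analysis already planned in section 2.11.1.

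If the full protocol already contains such an exception, print it in section 2.6. If the ban is kept without one, limit the conclusion to Chinese patent medicine added to a fixed background regimen.

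The cost is a few sentences. Drug name, dosage and usage are already recorded under section 2.6 and changes are already observed under section 2.7, so the main addition is the date of each change. The downside is that background therapy will vary somewhat more after baseline and may differ between groups, which is why it should be described by group.

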### Follow-up time point

2.7

Patients need to be hospitalized for 2 weeks as the introduction period and whether to enter the group is determined according to the treatment and medication conditions of the patients. The follow-up time points were 0th, 4th, 12th, 24th, and 48th weeks. The main curative effect, secondary curative effect, and concomitant medication changes of patients were observed.

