**Objective::**

It is hoped that the research method with higher evidential value will be adopted to compare the short-term, medium-term, and long-term effects of Chinese patent medicine combined with conventional western medicine and conventional western medicine alone in the treatment of CHD angina pectoris, so as to tap the clinical efficacy advantages of traditional Chinese medicine (TCM) and provide reliable data support for its clinical application.

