## Method

2

A prospective cohort study was conducted among patients with CHD angina pectoris who were treated with oral Chinese patent medicine and conventional western medicine. The patients were divided into exposed group and nonexposed group according to whether or not the patients with CHD angina pectoris were treated with Chinese patent medicine. The exposed group was treated with TCM combined with conventional western medicine, while the nonexposed group was treated with conventional western medicine alone. Patients need to be hospitalized for 2 weeks as the introduction period and whether to enter the group is determined according to the treatment and medication conditions of the patients. The follow-up time points were 0th, 4th, 12th, 24th, and 48th weeks. The main events, secondary events and adverse events were used as the evaluation criteria for clinical efficacy of CHD angina pectoris. In the experimental study, we will use strict indicators to detect standard operation procedure for multigroup and bacteria detection. It is hoped that the research method with higher evidential value will be adopted to compare the short-term, medium-term, and long-term effects of Chinese patent medicine combined with conventional western medicine and conventional western medicine alone in the treatment of CHD angina pectoris, so as to tap the clinical efficacy advantages of TCM and provide reliable data support for its clinical application. The technical route is shown in Figure 1.

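### Week 0 is not tied to admission or to the start of Chinese patent medicine, and prior users are not separated, so the baseline is not reliably pre-treatment and the effect from initiation is not cleanly estimable

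*Protocol article*

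**What the plan says.** All references are to the protocol article.

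- **Introduction period (2.7).** "Patients need to be hospitalized for 2 weeks as the introduction period and whether to enter the group is determined"; the basis for that decision is "determined according to the treatment and medication conditions of the patients". Follow-up is at weeks 0, 4, 12, 24 and 48. Week 0 is not defined by any clinical event.
- **Treatment in that period (2.6).** Patients "can be treated with the original scheme before admission during the study period". The purpose is also given: "the admission period is 2 weeks, so that the patient's condition is stable and meets the admission criteria".
- **Exposure (2, Method).** Groups are formed "according to whether or not the patients with CHD angina pectoris were treated with Chinese patent medicine". No start date or new-user rule is attached.
- **Eligibility (2.2.3, 2.2.4).** The four inclusion and nine exclusion criteria contain no washout and no rule on earlier use of Chinese patent medicine. Care setting is open: "For patients with angina pectoris of CHD in the inpatient department or outpatient department of cardiology".
- **Measurements (2.8.6).** The Seattle Angina Questionnaire (SAQ), examinations and omics samples are taken at weeks 0, 4 and 12. Adverse events are first listed at week 4.
- **Analysis (2.11.1, 2.11.2).** Baseline clinical characteristics are described as pre-treatment, and comparisons from before to after treatment are planned. Efficacy is also stratified by drug usage and treatment duration.
- **Objective (Abstract).** The study is to "compare the short-term, medium-term, and long-term effects of Chinese patent medicine combined with conventional western medicine" against conventional western medicine alone.

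**The concern.** A cohort comparison of a treatment needs three things to coincide: the point at which a patient qualifies, the point at which exposure is assigned, and the point from which outcomes are counted. Here qualification and exposure are settled through a stabilising hospital stay during which treatment continues, and the start of follow-up is left floating.

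Three consequences follow if some exposed patients began Chinese patent medicine before week 0:

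- Their baseline SAQ, examinations and samples already carry part of any early effect, so changes from week 0 are not changes from treatment start.
- Patients who have an infarction, an intervention, death or intolerance during the stay may not enter, or may have the event before counting begins.
- If Chinese patent medicine has any early effect, good or bad, being stable enough to enter means something different in the two groups. Covariate adjustment among those who entered cannot restore those who did not.

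The short-term objective is the most exposed to this. The Discussion nevertheless argues that bias in the data is small.

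**Working it through.** The plan gives no figure for this point, so the main check sets the sections side by side.

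**Step 1. Where can week 0 fall?** The text allows two readings.

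- *End of the introduction period.* This is the natural reading of 2.7, because entry is decided from treatment received. Anyone who took Chinese patent medicine before or during the stay then has an on-treatment baseline.
- *At or near admission.* Section 2.8.6 lists the routine admission examination at week 0, section 2.9 allows week 0 data to come from medical records, and 2.11.1 speaks of a pre-treatment baseline. Week 0 then precedes the entry decision by up to two weeks, and a patient must still qualify at the end of that time.

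**Step 2. What does each reading mean for each kind of patient?**

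| Patient | Week 0 at end of stay | Week 0 at admission |
|---|---|---|
| Starts at or after week 0 | Baseline is pre-treatment | Baseline is pre-treatment |
| Starts during the stay | Up to 2 weeks on treatment at baseline | Baseline is pre-treatment, but group is decided afterwards |
| Continuing user from before admission | On treatment for an unrecorded time | On treatment for an unrecorded time |
| Outpatient | No stay, so week 0 is undefined | No admission, so week 0 is undefined |

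The pre-treatment label in 2.11.1 fails for continuing users under both readings.

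**Step 3. Can events drop out?** Section 2.2.4 excludes acute myocardial infarction, uncontrollable symptoms and known allergy to the study drug. Section 2.8.4 makes acute myocardial infarction a main event and anaphylactic shock an adverse event. The same occurrence during the stay can therefore make a patient ineligible instead of being counted.

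**Step 4. How large could the loss of events be?** This is illustrative and covers precision only.

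Inputs: risks 0.072 and 0.059 (2.3); 6200 per group with 10% loss (2.3), so n = 6200 × 0.9 = 5580; two-sided α = 0.05 (2.11.2).

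Assumptions not in the document: the two risks run from admission over 2 + 48 = 50 weeks, and a share f of events falls in the first two weeks, equally in both groups.

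Power = Φ[(d − 1.96·SE₀)/SE₁], where d = (0.072 − 0.059)(1 − f), SE₀ = √(2p̄(1 − p̄)/n), SE₁ = √((p₁q₁ + p₀q₀)/n), p₁ and p₀ are the risks after multiplying by (1 − f), and p̄ is their mean.

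For f = 0.10: p₁ = 0.0648, p₀ = 0.0531, d = 0.0117, SE₀ = 0.00446, SE₁ = 0.00446. Power = Φ[(0.0117 − 0.00874)/0.00446] = Φ(0.66) = 0.747.

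| f | Power |
|---|---|
| 0 | 0.793 |
| 0.04 (2/50, constant rate) | 0.775 |
| 0.10 | 0.747 |
| 0.20 | 0.693 |
| 0.30 | 0.632 |

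The bias from selection or from an on-treatment baseline would need the share of continuing users, their time on treatment, and the early effect. The document gives none of these.

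**The case against.** **The timing is inferred.** No section dates the first dose or places week 0 at the end of the stay, and the permission to keep the original scheme sits under the rules on combined drugs and does not name Chinese patent medicine. This stands. A reader might infer that week 0 always follows the start of treatment, or that the exposed group consists of continuing, already stabilised users. The text supports neither, since it allows new and continuing users alike. What it shows is an unanchored week 0 and no rule that separates the two.

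**The short-term comparison survives.** SAQ at weeks 0, 4 and 12 and events after week 0 can be compared between groups. This also stands, so it would be wrong to say that the short-term effect cannot be measured. What is compromised is the effect from initiation in those who started earlier.

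**Both groups pass through the same period, and stability is part of the target population.** Starting follow-up at stabilisation is a recognised choice. This answers part of the concern: uncounted risk within a group must not be read as bias in the difference between groups. It does not answer the point that stability may be reached with Chinese patent medicine in one group and without it in the other.

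**Treatment duration is already a stratum.** Section 2.11.2 does plan this, and 2.7 tracks medication changes. Duration strata can describe continuing users among those enrolled, but they cannot supply an admission SAQ or count patients who never entered.

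**The article is condensed.** The case report form may hold a start date. That is possible, but the week 0 definition, the pre-treatment label and the care-setting conflict are matters of what the article itself states.

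**Conclusion.** The point holds in a limited form. Week 0 is not anchored to admission or to the start of Chinese patent medicine, entry follows a stabilising stay on continuing treatment, and prior users are neither excluded nor separated. For patients who began before week 0, the baseline is not pre-treatment, events or intolerance in the introduction period may go uncounted, and the short-term effect from initiation is not cleanly estimable. Comparisons between groups after week 0 remain valid as comparisons among those who entered, subject to the usual confounding of a cohort.

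Separately, admitting outpatients conflicts with the statement that patients need a two-week hospital stay. This needs no assumption.

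The size of the bias cannot be computed from the document. The power figures (0.793 falling to between 0.775 and 0.632) rest on an assumed 4% to 30% of events in the first two weeks, lost equally in both groups, and measure lost information only.

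**What to change.** 1. Define one week 0 for all patients: admission, or the enrolment visit for outpatients. Take the baseline SAQ, examinations and samples then.
2. Record the start date of Chinese patent medicine and any prior use, in both groups.
3. Record main events, deaths and withdrawals during the introduction period, and report them by treatment received, including for patients who do not enter a group.
4. Report new users and continuing users separately, at least as a prespecified sensitivity analysis beside the planned duration strata. Restricting the primary comparison to new users is a debatable trade-off, because it changes the population and the question, and it is not required here.
5. Reconcile sections 2.2.3, 2.6, 2.7, 2.8.6 and 2.11.1 on care setting, the introduction period, week 0 and the description of the baseline. Record care setting as a baseline variable.

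None of this changes treatment. The cost is protocol and case report form wording, slightly more data collection, and smaller strata. It has to be done prospectively, because a baseline not taken at admission and patients not logged at entry cannot be recovered in analysis.
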